# Full-endoscopic versus conventional microsurgical therapy of lumbar disc herniation: a prospective, controlled, single-center, comprehensive cohort trial (FEMT-LDH trial)

**DOI:** 10.1186/s13063-022-06892-8

**Published:** 2022-12-07

**Keywords:** Disc prolapse, Minimal-invasive, Randomized, Trial, Endoscopic, Spinal stenosis, Disc herniation

## Abstract

**Background:**

Lumbar disc herniation is one of the leading causes of chronic low back pain. Surgery remains the therapy of choice when conservative approaches fail. Full-endoscopic approaches represent a promising alternative to the well-established microsurgical technique. However, high-grade evidence comparing these techniques is still scarce.

**Methods:**

Patients presenting with lumbar disc herniation will be included. The intervention group will obtain full-endoscopic disc decompression, whereas the control group will be treated by microsurgical disc decompression. We will apply a comprehensive cohort study design involving a randomized and a prospective non-randomized study arm. Patients who do not consent to be randomized will be assigned to the non-randomized arm. The primary outcome will be the Oswestry Disability Index (ODI). Secondary outcomes involve the visual analog scale (VAS) of pain and the SF-36 health questionnaire. Furthermore, clinical characteristics including duration of hospital stay, operation time, and complications as well as laboratory markers, such as C-reactive protein, white blood cell counts, and interleukin 6 will be determined and compared.

**Discussion:**

This study will significantly contribute to the current evidence available in the literature by evaluating the outcome of the full-endoscopic technique against the gold standard for lumbar disc herniation in a clinically relevant study setup. Additionally, the study design allows us to include patients not willing to be randomized in a prospective parallel study arm and to evaluate the impact of randomization on outcomes and include. The results could help to improve the future therapy in patients suffering from lumbar disc herniation.

**Trial registration:**

This study was prospectively registered in The German Clinical Trials Register (DRKS), a German WHO primary registry, under the registration number: DRKS00025786. Registered on July 7, 2021.

## Administrative information

Note: the numbers in curly brackets in this protocol refer to SPIRIT checklist item numbers. The order of the items has been modified to group similar items (see http://www.equator-network.org/reporting-guidelines/spirit-2013-statement-defining-standard-protocol-items-for-clinical-trials/).

## Introduction

### Background and rationale {6a}

Lumbar disc herniation is one of the leading causes of chronic back pain and has a lifetime prevalence of up to 3.5% in under 35 years old patients in western countries [1]. In 45- to 55-year-olds, the prevalence increases to over 20% [2]. The pathophysiology includes traumatic or disease-related loss of integration of the annulus fibrosus with subsequent herniation of soft nucleus-pulposus material. This herniation results in a prolapse into the subligamentous or epidural space with or without nerve compression. The nerve compression leads to the development of pain, which the patients report on medical examinations (intermittent or chronic lumbar pain usually precedes the acute event of a herniated disc) [3]. Conservative therapy is the therapy of choice in over 80% of patients with a lumbar disc herniation as the first event. It is based on bed rest, pain medication, muscle relaxants, and the avoidance of bad posture. All conservative measures aim to improving symptoms [4]. If the conservative treatments are exhausted, if cone or caudal symptoms are present, or in the case of rapidly progressive and severe neurological deficits, surgical therapy is indicated. There are several surgical methods used to treat herniated discs effectively.

The standard operative therapy is microsurgical sequestrectomy using an operating microscope [5]. The use of microsurgical techniques has reduced tissue damage and its consequences [6]. Although this operative technique has proven itself in clinics, continuous optimization of the operative procedures should be attempted. The aim of a new approach must be to minimize the trauma and its negative long-term consequences.

Minimally invasive techniques can reduce tissue damage and its consequences. Endoscopic operations have become standard in many areas. The most widely used full-endoscopic procedure in patients with lumbar disc disease is transforaminal surgery [7]. Laser and bipolar cauterization can be used. The removal of the intra- or extraforaminal sequestered material is technically possible. The resection of the sequestered nucleus pulposus within the spinal canal, i.e., a retrograde resection performed intradiscally through the existing annular defect, has already been described [8]. Nevertheless, difficulties in adequately resecting herniated discs within the spinal canal cannot always be ruled out. With lateral access, the spinal canal can be better reached with continuous visualization. However, the bony circumference of the foramen and exiting nerve can limit labor mobility and excision. In addition, the pelvis and abdominal structures can block access. Therefore, there may be restrictions utilizing the transforaminal access. The full-endoscopic interlaminar approach was developed to treat pathological situations that could not be successfully performed with the transforaminal technique [9].

Based on the results of a recently carried out systematic review, the full-endoscopic discectomy is regarded as one of the most effective treatment methods, which is supposed to be on a par with the gold standard of microsurgical surgical procedures [7]. However, the authors requested further prospective randomized studies to validate the results. The advantages of the full-endoscopic approach compared to open and microsurgical surgical procedures were, among other things, less bleeding, fewer complications, and faster recovery or an early return to everyday life. At present, there is not yet sufficient evidence regarding iatrogenic muscle trauma in the comparative examination of the two methods. The comparison of muscle damage parameters (surrogate markers) in the blood of the treating patients could provide further information about the outcome of the existing therapies.

Furthermore, patient-oriented outcomes, such as the perception of pain and limitations in everyday life, are relevant and need to be evaluated in affected patients. Finally, the available evidence does not sufficiently report the surgeon’s experience level and the number of surgeons involved when comparing both techniques, representing a significant limitation [10, 11]. The study aims to compare the results of lumbar discectomies using the full-endoscopic technique via the interlaminar and transforaminal access with those of the conventional microsurgical technique, particularly with regard to iatrogenic muscle trauma and patient-related outcome measures. Notably, one surgeon who is highly experienced in both methods will perform the surgery. This investigation will take place as a “comprehensive cohort study,” including a randomized and non-randomized study arm comparing the endoscopic versus microsurgical decompression to provide a high level of evidence. Further, this approach allows us to evaluate the impact of randomization on study outcomes.

### Objectives {7}

We sought to compare the full-endoscopic versus microsurgical technique for the decompression of lumbar disc herniation, focusing on patient-reported outcome measures, clinical characteristics, and laboratory marker evaluations. Patient-reported outcome measures will be evaluated preoperatively, immediately postoperatively, after 24 h, 48 h, 3 weeks, 1 year, 2 years, and 5 years postoperatively to provide the necessary and currently lacking long-term data.

### Trial design {8}

We will perform a comprehensive cohort trial involving a randomized and a prospective non-randomized study arm, each including intervention (full-endoscopic surgery) and control (microsurgical decompression) groups (superiority framework). Patients who do not consent to be randomized will be assigned to the non-randomized arm. Figure 1 illustrates the study design.

**Fig. 1 Fig1:**
[figure not shown]
Illustration of the study design

## Methods: participants, interventions, and outcomes

### Study setting {9}

Patients will be recruited at the Loretto Hospital Freiburg, Freiburg, Germany. Surgery, evaluations, follow-ups, and data analysis will be performed at the same institution.

### Eligibility criteria {10}

Inclusion criteria:Gender: Both male and femaleMinimum age: 18 yearsMaximum age: 75 yearsPatients for whom the medical indication for lumbar disc surgery is given and conservative therapy was unsuccessful

Exclusion criteria:Patients under 18 years of agePatients incapable of giving consentPatients who contact the Loretto Hospital in advance with the request of one of the two surgical methods (these patients will be assigned to the respective non-randomized group if they consent to participate in the study)Patients who do not agree to follow-up appointments 3 weeks, 1 year, 2 years, and 5 years post-opBreastfeeding, pregnant, or childbearing women who plan to become pregnant while participating in the studyMassively sequestered disc prolapseProlapse in the upper lumbar region (L2 or above)Patients with previous prolapse and revision surgeryProlapse affects several segmentsPatients ≥ 120 kgPatients with an active infection processPatients with other serious, especially malignant, diseasesPatients with other severe spinal disorders, such as osteoarthritis, osteopenia, osteoporosis, or osteomalaciaPatients with congenital malformations of the spine

Eligibility criteria for the surgeon: Intervention will be performed by one spine surgeon with at least 5 years of clinical experience in both surgical techniques.

### Who will take informed consent? {26a}

Informed consent will be obtained from FH and GL. The informant consent includes an extensive explanation of the surgery, the study design, the pros and cons of the techniques, and a detailed description of how data are handled. Patients will further be informed that their participation in a non-randomized study arm is possible if they refuse to be randomized or already have a preference regarding the surgical technique. Patients will receive a copy of the patient informed consent and get sufficient time to solve their doubts.

### Additional consent provisions for collection and use of participant data and biological specimens {26b}

Not applicable as no additional biological specimens will be analyzed. Blood samples are regularly taken during surgery and postoperatively and do not require additional consent.

### Interventions

#### Explanation for the choice of comparators {6b}

We will compare the full-endoscopic disc decompression versus microsurgical disc compression for lumbar spinal stenosis. Our study aims to test the superiority of full-endoscopic decompression against the current gold standard.

#### Intervention description {11a}

Upon enrollment in this clinical study, medical history will be recorded, and patients will undergo a comprehensive medical examination. This includes, in particular, a physical examination, an assessment of pain and symptoms, a neurological examination, an x-ray of the lower back (lumbar spine), computed tomography, or magnetic resonance tomography (if not recorded otherwise in the 6 months before the date of the surgery). These imaging procedures are part of the conventional treatment for back operations at our hospital and are also carried out regardless of participation in the study. Patients will provide blood samples preoperatively, immediately postoperatively, and after 48 h postoperatively. These examinations are part of the conventional treatment for back operations and are also carried out in the hospital regardless of participation in the study. However, in addition to the blood markers usually obtained and assessed in the study (C-reactive protein, white blood cell count, creatine kinase), we will also include interleukin 6 as a marker for inflammation and tissue damage. Complication rates seen during the surgery and postoperative complications will be determined. Time of hospital stay will be recorded. Follow-up examinations will be performed in time intervals illustrated in Fig. 2. For patient-reported outcome measures (PROMs), patients will be asked to fill out the respective questionnaire in predefined time intervals at our hospital. The skin incision for the gold standard (microsurgical technique) is about 3 to 5 cm long and depends mainly on the length of the narrowed nerve path. The parts of the intervertebral discs that exert pressure on the nerves and/or the spinal cord are removed with special instruments advanced through a trocar (sleeve) or spreader until the herniated disc is reached. The operation is performed utilizing a surgical microscope. After removing all the instruments, the skin is sutured.

**Fig. 2 Fig2:**
[figure not shown]
Illustration of SPIRIT study timeline. Patient-reported outcome measures (PROMs), Oswestry Disability Index (ODI), SF-36 health survey, and visual analog scale (VAS) of pain

“Full endoscopic” means that the operation is carried out exclusively using an endoscope. The skin incision is about 0.8 and a maximum of 1 cm long. The parts of the intervertebral discs that exert pressure on the nerves and/or the spinal cord are removed with special instruments inserted through the working channel integrated into the endoscope until the herniated disc is reached. A camera is incorporated in the endoscope so that the operation is carried out under visual control. After removing all the instruments, the skin is sutured.

#### Criteria for discontinuing or modifying allocated interventions {11b}

Discontinuation of the intervention will be applied if the intervention failed to allow sufficient treatment of the pathology during surgery (switch to the microsurgical technique (“conversion”) and upon participants' request at any time.

#### Strategies to improve adherence to interventions {11c}

Our strategy to improve adherence to the follow-up monitoring includes a face-to-face adherence reminder session with the surgeon (FH) at the regular postoperative follow-up visits. Furthermore, we will ask patients during the visits how they can be best contacted (e.g., telephone, WhatsApp, SMS). The approach to remind patients to attend the follow-up visits for questionnaires will depend on their preferred way to be contacted.

#### Relevant concomitant care permitted or prohibited during the trial {11d}

Patients are asked to inform the doctor regarding newly diagnosed diseases potentially affecting the outcomes of interest. Decision on excluding patients suffering from relevant diseases that could affect outcome assessments will be performed by the surgeon (FH) after contacting the doctor who diagnosed the disease and discussion with at least two additional research members of the study.

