### Assignment of interventions: blinding

#### Who will be blinded {17a}

The researchers analyzing the final data will be blinded.

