#### Procedure for unblinding if needed {17b}

Not applicable as surgeons and patients will not be blinded.

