#### Methods in analysis to handle protocol non-adherence and any statistical methods to handle missing data {20c}

If lost to follow-up exceeds 20%, an intention to treat analysis will be performed, utilizing single imputation replacing the missing value with the mean of the respective variable.

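### The unblinded surgeon may exclude patients for newly diagnosed diseases, and nothing keeps those patients in the primary 1-year ODI comparison

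*Protocol article*

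**What the plan says.** Section {11d} of the protocol article opens with a reporting duty: "Patients are asked to inform the doctor regarding newly diagnosed diseases potentially affecting the outcomes of interest". It then gives the rule at issue: "Decision on excluding patients suffering from relevant diseases that could affect outcome assessments will be performed by the surgeon". The decision follows contact with the doctor who made the diagnosis and "discussion with at least two additional research members of the study".

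Four other sections bear on this rule:

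- **Eligibility criteria {10}:** "Intervention will be performed by one spine surgeon with at least 5 years of clinical experience in both surgical techniques". The person who decides is therefore the person who operated, in both groups.
- **Blinding {17a} and {17b}:** "The researchers analyzing the final data will be blinded", while "surgeons and patients will not be blinded".
- **Non-adherence and missing data {20c}:** "If lost to follow-up exceeds 20%, an intention to treat analysis will be performed".
- **Discussion:** endoscopic operations converted to microsurgery are analysed as endoscopic.

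The primary outcome is the ODI, with 1 year as the main time point (Outcomes {12}).

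**The concern.** A disease diagnosed during follow-up is, with few exceptions, an event after randomisation. Removing patients because of such events gives up the protection of randomisation unless removal is unrelated to both arm and outcome, and nothing in {11d} secures that. The trigger is relevance to outcome assessment, the judgement is made case by case, and the decider knows which operation was done. If more patients with poor ODI are removed from one arm than from the other, the difference moves in favour of the first arm.

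The other provisions do not close the gap. Blinded analysts receive the data after the exclusions have been made. The intention-to-treat sentence is conditional on the amount of loss, so with 20% loss or less nothing stated brings an excluded patient back. The rule on conversions concerns a different event.

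**Working it through.** **1. Is there a safeguard on the decision?**

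Section {5d} lists four research members, including the surgeon. The two or more colleagues consulted must, if drawn from that list, come from the other three: the one who assigns participants {16c} and the two who assess outcomes and manage data {21a}. Any two of these three include at least one outcome assessor. No section asks any of them to judge without knowledge of allocation or ODI. The consultation is real, but it is not a blinded one.

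**2. Is an excluded patient kept in the primary analysis?**

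| Section | What it covers | Covers {11d} exclusions? |
|---|---|---|
| {20c} | Intention-to-treat if loss exceeds 20% | Not at 20% or less |
| Discussion | Conversions analysed as allocated | No |
| {17a} | Blinding of final analysts | No, exclusions come earlier |

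**3. The plan's own sample size.**

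Inputs from {14}: expected difference 8, limit 4, SD 10, one-sided alpha 0.05, power 80%, drop-out 10%. The stated number follows with the squared denominator (8 − 4)²:

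n = 2 × (1.645 + 0.842)² × 10² / 4² = 77.3, so 78 evaluable per group; 78 / 0.9 = 86.7, so 87 per group and 174 in total, as stated.

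**4. Illustration of bias.**

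The documents give no exclusion rate, so the rates below are assumptions. Exclusions fall in the endoscopic arm only, a fraction f is removed, and the removed patients' ODI is g points worse than that arm's overall mean. The mean of those who remain improves by f × g / (1 − f). The standard error is held at 78 per arm: 10 × √(2/78) = 1.60. With a true advantage of exactly 4 points, type I error becomes 1 − Φ(1.645 − shift/1.60).

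| f | Patients of 78 | g | Shift (points) | One-sided type I error |
|---|---|---|---|---|
| 2% | 1.6 | 10 | 0.20 | 0.065 |
| 5% | 3.9 | 10 | 0.05 × 10 / 0.95 = 0.53 | 0.094 |
| 5% | 3.9 | 20 | 1.05 | 0.162 |
| 10% | 7.8 | 10 | 1.11 | 0.171 |

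**5. Upper bound.**

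Suppose the removed patients are exactly those with the highest ODI in one arm. For a normal ODI with SD 10 the mean shifts by 10 × φ(z) / (1 − f), where z is the upper-f normal quantile. This gives 0.70, 1.09 and 1.95 points for f = 3%, 5% and 10%, or 18%, 27% and 49% of the 4-point limit. No choice of patients from one arm gives a larger shift at the same f under this model.

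**6. Lower bound.**

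If exclusions are equal in the two arms and unrelated to outcome, the shift is zero. Power is Φ(4 / (10 × √(2/n)) − 1.645): 80.3% at 78 per arm, 78.5% at 74 and 76.5% at 70.

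**The case against.** The strongest reply is that the process is more careful than one surgeon striking names off a list. It starts with a patient's report, needs contact with an outside doctor and requires discussion with at least two colleagues. That is correct, and it lowers the chance of arbitrary exclusions. It does not make the decision blind, and the final call stays with the surgeon.

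A second reply is that the trigger is a disease, not an observed ODI value. This also stands. A reader might infer that exclusion is made on the outcome itself, but the text says only that the disease could affect outcome assessments. What is supported is that exclusion can be related to outcome.

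Third, {11d} gives no time point and does not say whether a patient leaves the trial or only the analysis. Exclusion between enrolment and surgery is possible too. Either meaning can cost the 1-year ODI, so the ambiguity does not help the plan. In the non-randomised arm there is no randomisation to break, although selective exclusion would matter there as well.

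Fourth, a reader might infer that harms of surgery would be removed as new diseases. The documents give no such case, and the section on harms {22} counts complications as secondary outcomes. It does not, however, separate a complication from a disease that could lead to exclusion.

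Finally, an analysis plan that is not shown may define the analysis set. The point here is a rule that the protocol states, together with a conditional intention-to-treat rule. A later plan could not recover ODI values that were never collected.

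**Conclusion.** The point holds in this form: {11d} permits unblinded exclusion for new diseases, mostly after randomisation, and no stated rule retains those patients in the primary 1-year comparison. This can bias the randomised comparison.

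It is tempting to conclude that the comparison will be biased, or biased in favour of endoscopy. The documents do not support that, because they give neither the number of exclusions nor their distribution between arms. Under the assumptions shown (one arm only, SD 10), a shift of about 0.5 points is plausible with some four exclusions of moderately worse patients, and type I error then nearly doubles, to about 0.09. The shifts of 0.70, 1.09 and 1.95 points are worst cases, not expectations. If exclusions have nothing to do with arm or outcome, there is no bias and power falls by a few percentage points at most over the range examined.

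**What to change.** Amend {11d} and {20c} together:

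- Remove exclusion after randomisation from the primary analysis. Every randomised patient is analysed in the allocated arm, whatever the amount of loss to follow-up.
- Continue ODI collection after a new diagnosis, and record the diagnosis with its date as an intercurrent event.
- If an analysis without such patients is wanted, make it a sensitivity analysis with a disease list fixed in advance. Those who judge the cases should be blind to both allocation and ODI. The two members who handle data also assess the outcomes ({18a}, {21a}), so hiding allocation from them would not be enough.
- For the non-randomised arm, apply the same rule of keeping all patients.

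The cost is a change of wording, and someone outside outcome assessment to judge cases if the sensitivity analysis is run. The statistical price is slightly more outcome noise in the primary analysis from intercurrent disease.
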